## Abstract

**Theoretical framework:**

Cigarette smoking is the leading preventable cause of death worldwide, with nicotine dependence notably common among individuals with Substance Use Disorders (SUD). Smoking exacerbates both physical and mental health issues, further complicating the treatment of SUD. Current therapeutic approaches for SUD often prove inadequate, indicating a need for new strategies. Recent advancements in metabolomics and gut microbiome research have provided valuable insights into the biological mechanisms underlying addiction, warranting further investigation.

**Objectives:**

This study aims to investigate the therapeutic potential of smoking cessation for individuals with SUD, using a Cognitive-Behavioral Therapy (CBT) six-week group intervention within a therapeutic community. The research specifically explores the psychobehavioral, metabolic, and gut microbiome domains. It is hypothesized that smoking cessation will improve emotional regulation self-efficacy and reduce substance craving, mediated by changes in metabolic and microbiome profiles linked to brain systems of affect and reward.

**Methods:**

A randomized controlled trial (N = 100) will be conducted, examining outcomes such as clinical relapse rates as well as microbial and metabolic markers, investigating pathways of short-chain fatty acids, oxidative stress and inflammation, lipid, tryptophan, and one-carbon metabolism. Participants will undergo a CBT smoking cessation intervention, with pre- and post-assessments, compared to a control group receiving treatment as usual. Metabolomic and microbiome analyses will be conducted using blood and stool samples, alongside psychological assessments via questionnaires. Covariate analyses will be undertaken to control for metabolic and gut microbial effects of long-term psychiatric medications (antidepressants, mood stabilizers, antipsychotics, and opioid substitutions) present in the sample. Behavioral assessments will be conducted at a 3-month follow-up. The study is registered at clinicaltrials.gov under NCT06803706.

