#### Gut microbiome pathways: SCFA, tryptophan, and bile acids

1.8.3

Few small studies have directly examined the effect of smoking cessation on the microbiome (67, 68), but there is a growing body of evidence for general smoking-associated gut microbial alterations (69). A large mendelian randomization study provided mechanistic insights for a cross-talk and causal relationship between bacterial species and smoking behavior. Fan et al. (28) reported that lower abundances of *Actinobacteria* may cause increased smoking, with a potential positive feedback effect (further lowered abundances of *Actinobacteria* by smoking). Bacterial species and also belonging metabolic pathways were identified: *Actinobacteria* and *Peptococcus* were associated with alterations in tryptophan and tyrosine metabolites, and *Peptococcus* with effects on valerate (a short-chain fatty acid SCFA). The authors concluded, that these bacteria, via the identified metabolites, play a causal role in the action pathway from the gut microbiome to smoking behavior (28).

Tryptophan metabolism, and the downstream kynurenine pathway is a key metabolic pathway in the broader addiction literature (70). It is known that drugs of abuse dysregulate tryptophan metabolism and kynurenine metabolite concentrations via oxidative stress and immune responses, with immediate effects on the dopamine reward system. A recent study provided additional evidence for disturbances of tryptophan and kynurenine metabolism through smoking (71). Disrupted kynurenine pathway metabolism was also found in depression (72), altogether pointing to shared pathways of affect and reward in addiction and other psychiatric conditions.

Short-chain fatty acids (SCFA) are produced by the bacterial fermentation of dietary fiber, and are known as key gut-brain signaling mediators with a high relevance for reward and addiction (73–75). SCFA are lowered in smokers via gut microbial effects (76). They have anti-inflammatory properties, protect against oxidative stress and modulate transcriptional regulation in the brain. SCFAs exert epigenetic effects, stimulating memory and synaptic plasticity by inhibiting histone deacetylases (HDAC) or modulating DNA methylation, thereby altering the expression of addiction- related genes (*e.g.*, CREB transcription factor, c-Fos, dopamine receptors and μ-opioid receptors) and persistently reshaping reward circuit plasticity (77).

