#### Metabolic domain

2.1.2

The notion of addiction as a metabolic disorder requires further investigation in human subjects and in the clinical field, which represents an emphasis of investigation in this study (14, 16). Analyses will be performed with regard to metabolic profiles in SUD patients during their inpatient-stay in a drug-free therapeutic community and the additional contrasting between-group effects of smoking cessation. While the examination of metabolic factors is largely exploratory, particular attention will be paid to metabolic markers and cluster analyses corresponding to psychiatric symptoms, as well as to pathways of choline and folate metabolism. Metabolic correlates of primary emotions and psychiatric symptoms will be identified in exploratory analyses. In line with previous research, we hypothesize that smoking cessation goes along with increased choline levels and altered choline/folate metabolism (14). Downstream analyses will be focused on metabolites of immune and inflammatory regulatory pathways, oxidative stress, neurotransmitter precursors and metabolites and enzymes (tryptophan, kynurenic and quinolinic acid, indoleamine-2,3-dioxygenase, and tryptophan-2,3-dioxygenase).

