A-priori sample size calculations were performed with G-Power (108) (version 3.1.9.6), for a mixed-design ANOVA with one interaction between group (2 groups) and assessments (2 repeated measurements). Considering the effects mentioned above, the mixed-design ANOVA was set rather conservatively for a medium effect size (Cohen’s F = 0.25), a statistical Power (1-β) of 0.9, a α of 0.05, an intra-correlation coefficient of 0.5 and nonsphericity correction of 1, resulting in a minimum sample size of 46 subjects per group, and a critical F = 4.06. Adjusting for expected attrition of about 10%, a total sample size of size of 100 is set. The many (mostly biological) variables measured in this study will expectably require statistical corrections; this will also be compensated by statistical methods exceeding classical linear approaches, namely machine learning feature detection and modelling methods (109).

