#### Controlling for potentially confounding variables, and multiple testing

4.7.3

Proper analysis of the research questions in the SUD sample will be hampered by several sources of variance, such as diet, psychiatric diagnoses, medications, and history of substance misuse. These variables will be held constant as control variables.

Psychiatric comorbidity is highly present in the population. Psychiatric symptom burden and classes of psychiatric diagnoses are associated with systematic metabolic and microbiome profiles (72, 113, 114). Classes of psychiatric secondary diagnoses (mood, anxiety, psychotic, and neurodevelopmental disorders) will therefore be considered as covariates. Intake of psychotropic medications are respectively frequent. The literature shows reciprocal interactions between psychotropic medications and gut microbiota (115), and metabolic patterns in response to treatment (116, 117). Type of medication class intake (antipsychotics, antidepressants, antianxiety drugs, anticonvulsants/mood stabilisers, opioid substitution) will be considered as covariates. Length and consumption patterns from SUD history will also enter covariate analysis (with regard to substances – primarily consumed substances vs. polytoxicomania). These covariates will be entered in Multi-omics factor analysis (MOFA) in direct joint modeling (118) to ensure that observed microbiome–metabolome–psychological associations are not driven by covariate effects. For the microbiome domain, intervention vs. control group comparisons regarding microbial abundance and composition will be performed with Analysis of Compositions of Microbiomes with Bias Correction (ANCOM-BC), a package which allows for continuous and categorical covariate adjustment within a linear regression framework, and was designed to analyze longitudinal data (119).

Metabolome and microbiome studies involve the examination and statistical testing of a multitude of variables. Thus, controlling for multiple testing is a must; False Discovery Rate corrections will be based on statistical recommendations promoting flexible algorithms within the R package FDRestimation (120).

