##### Nuclear magnetic resonance (NMR) pipeline

4.7.6.1

To quantify metabolites in serum and stool of the participants, the untargeted metabolomics analysis will be performed with state-of-the-art NMR (nuclear magnetic resonance). Nuclear magnetic resnonance (NMR) spectroscopy was selected over other metabolomics pipelines such as mass-spectrometry (MS-) based approaches. Liquid chromatography (LC-MS) and gas chromatography (GC-MS) allow for comprehensive, untargeted metabolome profiling and analyses of specific metabolic pathways (127). However, the strength of NMS spectroscopy is that it provides a robust and highly reproducible platform for metabolomics, offering inherent quantitative accuracy regarding analytical stability, quantitative reliability, and data consistency (128, 129). NMR is therefore well suited for a longitudinal study design, allowing for excellent comparability of groups and timepoints. Metabolome analysis will focus on gut bacteria metabolites such as SCFA (e.g., butyrate), processed nutrients like polyphenols, folate, tryptophan and kynurenine metabolites, and metabolites of biochemical energy-pathways. Furthermore, choline and folate levels, lipids, and metabolites of inflammatory pathways and oxidative stress will be analysed.

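### The one directional metabolite hypothesis, that choline rises after smoking cessation, has no dedicated test and is left to an FDR-corrected screen whose family is undefined

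*Protocol article*

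**What the plan says.** - **Targets.** The abstract lists areas of interest: "investigating pathways of short-chain fatty acids, oxidative stress and inflammation, lipid, tryptophan, and one-carbon metabolism". Section 1.8.3 gives background such as "SCFA are lowered in smokers via gut microbial effects". Only section 2.1.2 turns a metabolite into a directional hypothesis of the trial: "we hypothesize that smoking cessation goes along with increased choline levels and altered choline/folate metabolism". The same section, like section 2, describes this work as mainly exploratory.
- **Measurement.** Section 4.7.6.1 states that "the untargeted metabolomics analysis will be performed with state-of-the-art NMR", and lists choline and folate among the quantities this analysis covers, in blood and stool.
- **Test.** For plasma, section 4.7.6.3 plans univariate comparisons to find lipoproteins and metabolites that differ between groups. Table 2 lists PCA, O-PLS-DA and correlation for metabolite concentrations. Choline is singled out in neither place.
- **Multiplicity.** Section 4.7.3: "controlling for multiple testing is a must; False Discovery Rate corrections will be based on statistical recommendations promoting flexible algorithms". The family, the q level and the number of tests are not given, and no exception is made for a prior hypothesis.
- **Sample size.** Section 4.7.1 sizes the trial "for a mixed-design ANOVA with one interaction between group (2 groups) and assessments (2 repeated measurements"), with "a α of 0.05, an intra-correlation coefficient of 0.5 and nonsphericity correction of 1". It accepts that the many biological variables will need correction and expects machine-learning methods to compensate.

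**The concern.** A hypothesis with a stated direction and a single named analyte can be tested once, at the level used in the sample size calculation. As written, nothing in the analysis sections distinguishes choline from any other quantity in the NMR output. If it is corrected with the full panel, its significance threshold depends on how many features are assayed and how many of them happen to change. Neither has any bearing on whether choline changes. A null result could then reflect the size of the screen. Leaving the family open also means that it could be chosen after the results are known. The remark that machine learning will compensate does not help here, because feature detection does not restore power for one prespecified contrast.

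**Working it through.** **1. The plan's own figure.** Inputs from section 4.7.1: f = 0.25, two groups, two measurements, correlation 0.5, nonsphericity 1, alpha 0.05, power 0.90. For the within-between interaction, lambda = f² × N × m / (1 − rho), with 1 and N − 2 degrees of freedom.

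- N = 46 in total: lambda = 0.0625 × 46 × 2 / 0.5 = 11.5, critical F(1,44) = 4.06, power 0.912.
- N = 92 in total: lambda = 23, critical F(1,90) = 3.95, power 0.997.

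The printed critical F of 4.06 therefore belongs to 46 in total, not to the stated 46 per group. That is a separate discrepancy. It matters here because it explains why power at f = 0.25 is so high with the planned 100.

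**2. A common scale.** With 10% attrition, 100 × 0.90 = 90, or 45 per arm. At correlation 0.5 the SD of a change score is sqrt(2 × (1 − 0.5)) = 1 cross-sectional SD. With d the between-group difference in change, the two-group test has noncentrality d² × N/4. The interaction test has f² × N × 2/0.5 = 4f² × N. So d = 4f, and f = 0.25 means d = 1.0.

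**3. Choline tested alone at two-sided 0.05** (noncentral F, N = 90; z = d / sqrt(2/45)):

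- d = 0.5: z = 2.37, power 0.65
- d = 0.73: z = 3.46, power 0.93
- d = 1.0: z = 4.74, power 0.997

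The 0.73 is the only metabolite effect in section 4.7.1. It is for N-acetylputrescine in smokers versus former smokers, not for choline. The 0.5 is an assumption.

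**4. Choline inside a panel.** Not in the document, so assumed: 150 features, independent two-sided normal tests, Benjamini-Hochberg at 5%, every changed feature moving by the same d. If choline alone changes, the threshold is essentially 0.05/150 = 0.00033 (z = 3.59). Closed form: at d = 0.5, Φ(2.37 − 3.59) = 0.11; at d = 0.73, Φ(3.46 − 3.59) = 0.45. Simulated power for choline:

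| Features truly changed | d = 0.5 | d = 0.73 | d = 1.0 |
|---|---|---|---|
| choline only | 0.12 | 0.45-0.46 | 0.88 |
| 10% | 0.20 | 0.71 | 0.97 |
| 20% | 0.28 | 0.80 | 0.99 |
| about a third | 0.36-0.37 | 0.85 | 0.99 |
| 40% | 0.39 | 0.87 | 0.99 |

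The ranges for other panel sizes run from choline only to 40% changed. With 40 features they are 0.20-0.40 at d = 0.5 and 0.60-0.86 at d = 0.73. With 300 features they are 0.08-0.39 and 0.38-0.87. At d = 1.0 the range over panels of 40 to 300 is 0.84-0.99. Choline tested alone has the higher power in every cell.

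**5. A wider candidate family.** Assume 25 named metabolites (five per pathway, correlation 0.3 within a pathway), one pathway affected by 0.5 SD, and a baseline-adjusted test with SE = sqrt(2 × 0.75/45) = 0.183 SD. The chance of at least one hit in that pathway, pooled 150-feature panel versus own family of 25, is:

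- no other feature moves: 57% v 81%
- 20% of the other features move: 86% v 81%
- 40% of the other features move: 93% v 80%

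The separate family wins when signals are sparse and loses when they are common.

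**The case against.** **The pooled family is an inference.** A reader might conclude that the plan tests all named targets in one panel-wide FDR family. It does not say so; section 4.7.3 leaves the family undefined. This stands, and the power figures are conditional on pooling.

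**Family definition is normally SAP content.** This stands in part. Silence on the families would be no finding by itself. But the article does set out the multiplicity method and the metabolite analyses, and none of them provides for the hypothesis in section 2.1.2. A reserved test is a concrete change to a stated method.

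**Most named pathways and taxa are not hypotheses.** A reader might extend the point to all five pathways and the bacteria in section 1.8.3. The documents do not support that: those are background or areas of focus in work described as mainly exploratory. The microbial hypothesis on diversity has its own low-dimensional tests, namely alpha-diversity indices and db-RDA in section 4.7.5. The point is confined to choline.

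**The loss may be small.** At f = 0.25 it is, which supports the sponsor's view that the calculation was "the mixed-design ANOVA was set rather conservatively for a medium effect size". However, f = 0.25 is d = 1.0 on the change score, above the d ≈ 0.73 and d ≈ 0.70 cited in section 4.7.1. The 0.73 contrasts smokers with former smokers, and a randomised comparison in which some do not quit would be diluted.

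**A baseline-adjusted test would look better.** Choline alone at 0.5 SD would then have z = 0.5/0.183 = 2.74 and power 0.78. The planned 2 x 2 interaction is not baseline-adjusted, so 0.65 is the figure to use.

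**Conclusion.** The point holds for choline. The plan states one directional metabolite hypothesis and gives it no test of its own. If it is corrected with a 150-feature panel, power falls from about 0.65 to 0.12-0.37 at 0.5 SD, and from 0.93 to 0.45-0.85 at 0.73 SD. The low end is choline changing alone and the high end is about a third of the panel changing. At f = 0.25 the loss is minor. These figures rest on 45 evaluable per arm, correlation 0.5, independent tests, Benjamini-Hochberg at 5% and an assumed panel size. Two broader conclusions are not supported: that the named pathways and taxa in general lose much of their power, and that a separate candidate family is always more powerful. The first treats background text as hypotheses and assumes a pooled family; the second is true only when few features change.

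**What to change.** In section 4.7.3, name the group-by-time contrast in choline as a single prespecified test at two-sided 0.05, outside the FDR screen. Fix one specimen type for it before any sample is assayed. The text needs this choice because stool is also measured, and blood is called serum in section 4.7.6.1 but plasma in sections 4.4.3 and 4.7.6.3. Keep the remaining metabolites and taxa in the FDR-corrected screen, state the q level and which tests form a family, and label the results exploratory.

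A separate FDR family for the other named pathways is optional. If it is wanted, fix its members in advance and acknowledge that it can lose power when many features change.

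The change costs a few sentences and no extra patients or assays. The statistical price is one additional test at 0.05 outside FDR control, which means a 5% chance of a false positive if choline does not change.

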**Level of originality:**

This research will enhance our understanding of the complex interplay between smoking and mental health, offering potential for more effective treatment strategies for SUD. The current study’s focus on connections between metabolic and gut microbiome pathways with affect and reward is expected to yield valuable insights into addiction mechanisms and improve diagnostic and therapeutic practices.

**Clinical trial registration:**

## Smoking cessation in substance use disorder: metabolome and microbiome mechanisms, therapeutic barriers, and effects on emotion and reward processing

1

### Novel treatment approaches and improved outcomes in SUD are required

1.1

Cigarette smoking is the main preventable cause of death worldwide (1). Substance Use Disorder (SUD) is a psychiatric condition and goes along with dramatically reduced physical health and life expectancy (2), severe mental health problems (3), increased risk for suicide (4, 5) and high societal costs (6).

Besides apparent detrimental effects on physical health, smoking also contributes to reduced mental health and well-being (7), and it increases the propensity for the use of other substances (8). In line with this, nicotine dependence is highly prevalent in individuals with other SUD. Between 74% and 98% of those with SUD are also smokers (9, 10) and it is often observed that patients with SUD who overcome their primary addiction eventually die from a tobacco-related illness (11).

This situation also reflects the insufficiency of current treatment options in SUD, which are considered ineffective for too many individuals (12). With rising numbers of individuals diagnosed with SUD and societal costs worldwide over the past decades, the improvement of treatment outcomes and the management of SUD is therefore considered an important public global health priority (13).

### Metabolic and gut microbial mechanisms in SUD

1.2

Investigating metabolic and gut microbiome mechanisms holds promise for advancing the field (14, 15). Metabolomics, as the investigation of the metabolites present in an organism, may provide a better understanding of psychiatric processes, including the mechanisms of craving and relapse in SUD (12, 16, 17). SUD, in particular, can be conceptualized as metabolic disorders, as exposure to virtually any addictive substance has an impact on the metabolism of the organism, ranging from central impact on organs such as the gastrointestinal system and the liver up to energy turnover on different (intra- and extracellular) levels, going along with effects on signalling and transmitter systems in the brain (14, 16).

The conceptualization of SUD as a metabolic disorder originates from innovative forms of management of narcotic addiction in the 1960s, when Dole and Nyswander found out that relapse can be overcome in many cases by compensation of the underlying metabolic aberrances through methadone maintenance, enabling a return to normal work and relationship functioning (14, 18). With ongoing advances in the field, recent studies were able to match metabolic profiles with clinical phenotypes and subtypes of opioid addiction, introducing potential for the development of new treatment and management strategies (19).

The consideration of gut microbial factors and their consequences for brain signalling and metabolism, also referred to as the microbiota-gut-brain axis, is a complementary perspective in this context (12, 15, 20). The insight that the microbiome shapes host metabolic, immune, endocrine, as well as central and autonomous nervous functions has led to a paradigmatic shift in neuroscience (21–25). Gut microbiota are integral agents in the metabolic processes of the human body. In detail, relevant classes of metabolites as well as the bacterial taxa involved in their production and proliferation, have been identified. Among others, gut bacteria-associated metabolites, such as short-chain fatty acids (SCFAs), polyunsaturated fatty acids (PUFAs), bile acids, and those involved in tryptophan metabolism, are highly relevant to psychiatric processes (20, 26). These metabolites affect energy turnover in the brain, as well as signalling and transmission, development, inflammation, and protection of brain tissue, as well as the permeability and integrity of the blood-brain barrier.

Metabolic and gut microbial mechanisms in addictive processes were identified in a broad range of relevant substances with regard to SUD, such as nicotine (27, 28), alcohol (29–31), amphetamines and psychostimulants (32, 33), cocaine (34, 35), and opioids (17, 19). Importantly, the current understanding of SUD and addiction in general is not limited to the biological dimension but – following the biopsychosocial model- takes into account psychological as well as social factors and interventions (36, 37). This enables meaningful research through the combined study of psychological interventions, as well as metabolome and microbiome perspectives and methods, as demonstrated by pioneering studies (38, 39).

